**10. Termination and Early Discontinuance of Testing**

Early discontinuance of testing is considered to be a situation where a portion or the entirety of the testing is discontinued ahead of schedule for any one of the following reasons:

1. The effectiveness or ineffectiveness of the treatment being tested is verified at an early stage.
2. It is determined early on that there is little likelihood of proving the effectiveness of the treatment being tested.
3. It is determined that there is a problem with the safety of the treatment being tested or the control treatment, based on an event report of a seriously harmful illness or on data outside of the aforementioned clinical testing.

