**3. Study Design**

・Using a random number table created by free-software R (http://www.r-project.org), the patients were randomly assigned to the AKA-H (AKA-H) or the sham (S) groups.

・This study was a parallel group comparison in which the AKA-H group and S group were compared for 6 months. The study was randomized at the level of the individual patient, and it was a single-blind RCT in which only the patients were blinded to the details.

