**・Randomization**

Output 0 or 1 in order using a random number table created free-software R (for example, 0 for the first person, 1 for the second person, and 1 for the third person). A piece of paper with 0 on it is enclosed in an envelope with 1 on it, and the envelope is sealed. A piece of paper with 1 on it is enclosed in an envelope with 2 on it, and then the envelope is sealed. This procedure will be done by a nurse in the outpatient department. The nurse will keep and store the envelopes without being informed of the purpose of creating those envelopes so that the first author cannot be involved in the randomization. At the patient’s first visit, a nurse will bring an envelope with the number corresponding to the patient number to the first author after the patient walks in the outpatient medical examination room. Then, the first author opens the envelope to provide sham procedure or AKA-H after confirmation of the number without informing the patient. Caution is needed to have the patient not recognize which procedure will be performed.

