**5. Outcomes and Confidentiality**

Primary outcome and secondary outcomes

- Primary outcome is mean VAS score over a month from the previous visit.
- Participants are required to record their VAS score in a form every day at almost the same time for at least 1 month until the first visit and bring the recorded form along with consent form at the first visit.
- Secondary outcomes are Roland-Morris Disability Questionnaire (RDQ) and 36-Item Short-Form Health Survey (SF-36).
- Participants will fill RDQ and SF-36 at every visit including the first visit at the waiting room by advance reservation only before seeing a doctor. Participants are required to visit the outpatient office once a month, in principle, for 6 months after initiation of treatment.
- A VAS record form will be collected at every visit, and a new one will be provided to the participants.
- RDQ and SF−36 will be filled at the waiting room and will be collected at every visit. Those collected record forms will be stored in the locked locker at outpatient department.

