**6. Statistical Analysis**

- All statistical analyses were performed using the principle of intention-to-treat analysis.
- For missing data, the data were analyzed by extrapolating the last observation.
- A two-way (time period and treatment group) repeated measures analysis of variance will be used to observe the difference in data between the two groups during the intervention period.

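### Section 10 lets the trial stop once effectiveness is shown early, but the protocol sets no significance level, looks, boundary or patient number, so no type I error level is protected

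*Protocol*

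**What the plan says.** Protocol section 10 defines early discontinuance as the case where "a portion or the entirety of the testing is discontinued ahead of schedule for any one of the following reasons". Three reasons follow:

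- Reason 1: "The effectiveness or ineffectiveness of the treatment being tested is verified at an early stage".
- Reason 2: "It is determined early on that there is little likelihood of proving the effectiveness of the treatment being tested".
- Reason 3: a safety problem.

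Section 6, the whole statistical section, has three items: intention-to-treat, carrying the last observation forward, and the test: "A two-way (time period and treatment group) repeated measures analysis of variance will be used to observe the difference in data between the two groups". It does not mention interim analysis, a significance level or sidedness. The primary outcome in section 5 comes without a target difference or standard deviation: "Primary outcome is mean VAS score over a month from the previous visit". No planned number of patients, power or recruitment closing date appears in the text available.

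On access to data, section 3 says "it was a single-blind RCT in which only the patients were blinded to the details". The Randomization paragraph of section 4 has the first author open each envelope and give the procedure. Section 5 says "A VAS record form will be collected at every visit, and a new one will be provided to the participants"; the RDQ and SF-36 are also collected at every visit.

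**The concern.** Effectiveness can be shown early only by comparing the arms on accumulating data. Section 10 therefore authorises ending the trial on a favourable comparison, and sets no limit on how often the comparison is made or how strong it must be. This is a rule that the protocol states, so it is more than detail left for later.

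Two features make it matter more here. First, there is no stated number of patients, so the text offers nothing against which to judge whether a stop was early. Second, the person giving the treatment knows every allocation while outcome forms arrive monthly, and nothing in the text keeps that person from comparing the arms.

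If the trial stopped on a high point of the observed difference, the repeated measures analysis of variance would be read as a single test at a fixed sample size, which it would not be. False positives would exceed the nominal level, and the estimated effect of AKA-H would tend to be too large.

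**Working it through.** **Plan's own figure.** There is none to reproduce. The protocol gives no sample size, power, significance level, target difference or standard deviation. What follows illustrates what the clause permits.

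**Assumptions, none from the protocol.** The test statistic is approximately normal; K looks are equally spaced in information; the same unadjusted two-sided level is used at each look; the trial stops at the first crossing. The main case is 5% (critical value 1.96), with 1% and 10% as a range.

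**Formula.** Under no treatment effect, the statistics Z₁,…,Z_K are jointly normal with mean 0, variance 1 and corr(Z_i, Z_j) = √(i/j) for i ≤ j. The overall type I error is

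1 − P(|Z₁| < c, …, |Z_K| < c).

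**Two looks at 5%.** The correlation is √(1/2) = 0.707 and c = 1.96, so the overall error is 1 − P(|Z₁| < 1.96, |Z₂| < 1.96) = 0.0831.

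**Range.** Computed by numerical integration:

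| Level per look | 1 look | 2 looks | 3 looks | 5 looks |
|---|---|---|---|---|
| 1% | 1.0% | 1.8% | 2.4% | 3.3% |
| 5% | 5.0% | 8.3% | 10.7% | 14.2% |
| 10% | 10.0% | 16.0% | 20.2% | 26.0% |

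With two or more unadjusted looks, the overall error exceeds the nominal level in every row, so the direction does not depend on assuming 5%.

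**What a rule would look like.** For one look at half the information and an overall two-sided 5%, an O'Brien-Fleming-type spending function spends 4 × [1 − Φ(2.2414/√0.5)] = 4 × [1 − Φ(3.170)] = 0.0031 at the interim (critical value 2.963). Solving for the final critical value that brings the total to 0.05 gives 1.969, which is p < 0.0490. Check: 0.003 at the interim and 0.049 at the end give an overall error of 0.0500.

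**Which reasons are implicated.** A false positive requires an efficacy claim. Ending the trial for ineffectiveness (the other half of reason 1) or for little prospect of success (reason 2), with no efficacy claim, removes chances to reject and cannot raise type I error. It costs power. Only the word effectiveness in reason 1 produces the inflation shown.

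**The case against.** The strongest reply is that section 10 is a general termination clause. It schedules no look, and a statistical analysis plan or monitoring charter not shown here may hold the boundary. That stands in part. Looks and thresholds are often set outside the protocol, and their absence alone would not be a finding. But the clause permits an efficacy stop without referring to any such rule, so it would need amending even if another document restricted it.

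Four stronger readings are tempting and are not supported:

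- **That a stated 5% error rate is breached.** The protocol states no significance level, p-value or confidence interval. The 5% is an assumption made here.
- **That this trial's false-positive rate is one of the tabulated figures.** No interim analysis is planned, and nothing equates showing effectiveness with nominal p < 0.05.
- **That only section 10 decides when enrolment ends.** Section 10 presupposes a schedule, and section 7 says implementation schedules go to the ethics committee. Those are not shown. The supportable statement is that the protocol text available gives no number or closing date.
- **That the first author monitors results by arm.** Section 5 has the forms stored in a locked locker and does not say who tabulates them; section 12 mentions biometricians and data managers. The text shows the opportunity and no barrier to it, and no more than that.

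**Conclusion.** The point holds in this form: section 10 permits stopping for effectiveness, and the protocol text available gives no significance level, look schedule, boundary or number of patients to constrain it. A stop under that clause would protect no type I error level and would tend to overstate the effect. Under an assumed two-sided 5% at equally spaced unadjusted looks, the overall error is 8.3%, 10.7% and 14.2% for 2, 3 and 5 looks. These figures show the size of the risk that the clause opens; they are not a property of a planned procedure. A reader might also infer that the futility and ineffectiveness reasons must go. They need not, because they do not raise type I error. A boundary in an unseen analysis plan would reduce the risk, but the protocol would still permit what that plan restricts.

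**What to change.** 1. In section 10, remove effectiveness from reason 1.
2. In section 3, state a fixed total number randomised or a fixed recruitment closing date.
3. State that no between-arm comparison of VAS, RDQ or SF-36 for efficacy is made before the last patient's seventh-month evaluation.

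If early stopping for benefit is wanted, replace items 1 and 3 with one pre-specified efficacy look at half the information, using an O'Brien-Fleming-type boundary (about p < 0.003 at the interim and p < 0.049 at the end, for an overall two-sided 5%). A biometrician should run it, not the treating author. Item 2 is still needed, because half the information has no meaning without a planned total.

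The futility reason may stay, with any futility stop treated as non-binding and carrying no efficacy claim. Reason 3 on safety is untouched.

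The cost is an amendment to sections 3 and 10 with ethics committee approval, as section 9 requires. The downside is that the freedom to stop early for benefit is given up or restricted.

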**11. Preservation of Records**

The data collected shall be stored until the research representative completes this study or until at least one year to the day from the completion of the study. The medical institution conducting the study shall retain records for the longest period of time authorized (items such as medical examination and treatment records) along with documents stored at the medical institution conducting the study (items such as plans for implementing the study and informed consent documents).

**12. Attribution of Findings and Publication**

- UMIN Clinical Trials Registry, etc. will be conducted based on directives from ICMJE.
- Biometricians and data managers will be included as collaborators during the announcement of results.
- Provisions for the order of authors according to the order of the number of registered medical cases as well as provisions for corresponding authors will be conducted in advance.

**13. Appendix files**

- Pain scale and Recording paper
- Description document and consent form
